## Abstract

**Background:**

Up to 70% of people diagnosed with upper gastrointestinal (GI) tract or hepato-pancreato-biliary (HPB) cancers experience substantial reductions in quality of life (QoL), including high distress levels, pain, fatigue, sleep disturbances, weight loss and difficulty swallowing. With few advocacy groups and support systems for adults with upper GI or HPB cancers (i.e. pancreas, liver, stomach, bile duct and oesophageal) and their carers, online supportive care programs may represent an alternate cost-effective mechanism to support this patient group and carers. *iCare* is a self-directed, interactive, online program that provides information, resources, and psychological packages to patients and their carers from the treatment phase of their condition. The inception and development of *iCare* has been driven by consumers, advocacy groups, government and health professionals. The aims of this study are to determine the feasibility and acceptability of *iCare,* examine preliminary efficacy on health-related QoL and carer burden at 3- and 6-months post enrolment, and the potential cost-effectiveness of *iCare,* from health and societal perspectives, for both patients and carers.

**Methods and analysis:**

A Phase II randomised controlled trial. Overall, 162 people with newly diagnosed upper GI or HPB cancers and 162 carers will be recruited via the Upper GI Cancer Registry, online advertisements, or hospital clinics. Patients and carers will be randomly allocated (1:1) to the *iCare* program or usual care. Participant assessments will be at enrolment, 3- and 6-months later. The primary outcomes are i) feasibility, measured by eligibility, recruitment, response and attrition rates, and ii) acceptability, measured by engagement with *iCare* (frequency of logins, time spent using *iCare*, and use of features over the intervention period). Secondary outcomes are patient changes in QoL and unmet needs, and carer burden, unmet needs and QoL. Linear mixed models will be fitted to obtain preliminary estimates of efficacy and variability for secondary outcomes. The economic analysis will include a cost-consequences analysis where all outcomes will be compared with costs.

**Discussion:**

*iCare* provides a potential model of supportive care to improve QoL, unmet needs and burden of disease among people living with upper GI or HPB cancers and their carers.

**Australian and New Zealand Clinical Trials Registry:**

ACTRN12623001185651. This protocol reflects Version #1 26 April 2023.

## Background

Managing cancers is a significant public health and economic challenge. Healthcare costs in Australia directly attributable to cancer were $10.1Billion Australian dollars in 2015–16 [1]. There is also a growing body of evidence indicating timely access to supportive care, such as targeted information and support, can lead to improvements in quality of life and survival, as well as being cost-effective [2]. However, people living with upper gastrointestinal (GI) cancers and hepatic-pancreas-biliary cancers, in contrast to cancers with a higher public profile (i.e. breast and prostate), receive minimal support services [3].

Upper gastrointestinal (GI) cancers affect the upper digestive system and include the stomach and oesophagus. Hepato-pancreato-biliary cancers (HPB) affect the liver, pancreas and bile duct. Most recent data from the Australian Institute of Health and Welfare (AIHW) suggests the incidence of upper GI and HPB cancers in Australia is on the rise [4], with nearly 30,000 Australians diagnosed with one of these cancers each year, representing 555 new diagnoses each week [4]. Survival for upper GI and HPB cancers is low compared to more common cancers, with 5-year survival rates ranging from less than 10% to 40% depending on the cancer type [5]. In addition, up to 70% of people with these cancers experience substantial reductions in quality of life, with many living with high distress levels, ongoing pain, fatigue, sleep disturbances, unintentional weight loss and difficulty swallowing [6–8]. Interventions that can improve the QoL of those living with upper GI or HPB cancers are needed [9].

Informal carers of people living with cancer are an important component of the care team, playing a significant role in enabling patients to manage their disease, treatment and side effects outside of clinical settings [10, 11]. They are often a friend or family member who are differentiated from formal, professional caregivers within the healthcare team [12].

Previous research has highlighted the demands of caring for a person with cancer. This may be so overwhelming that providing care erodes the physical and psychological health of the carer [13]. In Australia, about 60% of the lifetime financial cost of cancer is borne by informal carers [14]. Despite the extensive involvement of informal carers in the management of people with cancer, there are limited support services for carers of people living with cancer in general, with few, if any, evidence-based solutions available to support carers of people with cancer [15, 16]. Recent studies have identified the need for more work to test interventions to support carers of people living with less common cancers [17] with interventions designed to improve mental health particularly needed for carers of people with advanced cancer [18].

Technology-based approaches can be specifically designed to bring evidence-based information from diverse sources and can provide tailored information and support for people affected by cancer [19, 20]. Such approaches can empower people with cancer and their carers, and provide a strong support tool for patients with complex health conditions [21]. Web-based interactive portals can be a cost-effective and user-centred strategy to provide support over the long term, as information and supportive care strategies can be accessed when they are needed rather than when a health professional is available. There is a strong imperative to determine whether web-based portals are effective and cost-effective in improving health outcomes for people affected by complex health conditions, such as those living with upper GI or HPB cancers.

Previous studies have identified that education, information, and tracking systems are needed to promote self-management for people with gastric cancers [22]. To our knowledge there are no current digital health interventions that incorporate information, online psychological programs, and access to community resources to support people diagnosed with upper GI and HPB cancers and those caring for them.

*iCare* has been developed to address the gap in support for people with upper GI and HPB cancers. The content and structure of the program were developed through consultation with our partner organisations and consumers and include links to information, resources, and access to psychological programs. The portal was pilot tested involving a sample of 10 patients and carers [23]. All participants reported *iCare* was acceptable and useable, with comments such as ‘*this is very valuable; there’s a lack of information and resources available’*; ‘*the portal is easy to use;’ ‘good for carers to feel supported too’;* ‘*a platform like iCare that provides ongoing support would be great’; ‘the carer is a huge part of the patient’s journey and it is important to include carers with this platform’, and ‘it’s important to advocate’.*

## Methods and analysis

### Primary aim

To determine the feasibility and acceptability of *iCare* for people living with upper GI or HPB cancers, and their carers. Feasibility, i.e. eligibility, recruitment, response and attrition rates; and acceptability, i.e., engagement with *iCare*, including frequency of logins, time spent use of the program and different features over the intervention period.

### Secondary aims

2.To examine the preliminary efficacy of *iCare* on people living with upper GI and HPB cancers QoL, using the Functional Assessment of Cancer Therapy – General (FACT-G) Scale; [24] and unmet needs, using the Supportive Care Needs Survey (SCNS) [25], at 3- and 6-months post enrolment;
3.To examine preliminary efficacy of *iCare* on carer burden, using the Zarit Burden Short Form 12 (ZBI-12) scale [26], unmet needs, using the Partner and Caregiver Supportive Care Needs Survey (SCNS-P&C) [27]; and QoL, using the Caregiver Quality of Life Index-Cancer (CQOLC) scale [28], at 3- and 6-months post enrolment;4.To explore the potential cost-effectiveness of *iCare* from health and societal perspectives, at 3- and 6-months post enrolment, for both patients and carers;5.To undertake a process evaluation, guided by the RE-AIM Framework [29], conducted in parallel with the RCT.

### Study design

The design is an Australian based phase II randomised controlled trial (RCT) where people diagnosed with upper GI or HPB cancers and their carers will be recruited and allocated (1:1) to receive *iCare* or usual care during a 3-month period. The time period recognises patients’ complex physiological and psychological needs and carer support needs, with outcomes, measured at enrolment (Time 1), 3 months (Time 2) and 6 months post-enrolment (Time 3, Fig. 1).

**Fig. 1 Fig1:**
[figure not shown]
Schedule of questionnaires * Functional Assessment of Cancer Therapy (FACT-G); Supportive Care Needs Survey (SCNS); Zarit Burden Interview-12 (ZBI-12); Partner and Caregiver Supportive Care Needs Survey (SCNS-P&C); Caregiver Quality of Life Index-Cancer (CQOLC); AQoL-4D (Assessment of Quality of Life – 4 Dimensions); SILS (Single Item Literacy Scale), Upper Gastrointestinal Cancer Registry (UGICR)

### Selection criteria

Patients will be eligible if they are:

aged 18 years or olderdiagnosed with upper GI or HPB cancers in the previous 4 monthsexpected minimum survival of 6 monthsable to speak and read Englishaccess to a web-based device, such as a smartphone, tablet, laptop, desktop computer or other internet connected device.

Carers will be eligible if they:

identify as a person involved in the day-to-day care and medical appointments of someone with upper GI or HPB cancerare aged 18 years or older andhave access to a web-based device, such as a smartphone, tablet, laptop, desktop computer or other internet connected device.

### Setting

#### Upper gastrointestinal cancer registry

Participants will be recruited primarily from the Upper Gastrointestinal Cancer Registry (UGICR) [30]. The UGICR is a clinical quality registry that receives an average of 830 reported Upper GI and HPB cancer cases each year. The Registry receives notifications of people diagnosed with these cancers from state-based cancer registries, individual hospital or surgical centres, pathology providers, and private clinicians’ rooms and after contacting people to allow them to opt out of the registry, the registry collects information on the diagnosis, treatment and outcomes of individuals with these cancers with a view to improve patient outcomes and quality of care. In general, people with our eligible cancers are registered with the UGICR within 3 months of diagnosis. 

People registered with the UGICR will be screened for study eligibility by registry staff, with those eligible sent a letter from the UGICR inviting them to participate in the trial. The invitation letter will also invite carers into the study. We aim to recruit patient-carer dyads, however, if one member of the dyad chooses not to participate, the other will still be eligible to participate in the trial.

Interested individuals (patients and/or carers) will use a Uniform Resource Locator (URL) or Quick Response (QR) code to access the study website to obtain more information, to register and to complete the first survey. UGICR letters will also include the contact details of the project manager and potential participants can email or call for further information.

If no response is received within 2 weeks, a follow-up invitation phone call will be made by registry staff to people who met the eligibility criteria.

#### Social media and clinical recruitment

Recruitment will be monitored weekly; if UGICR recruitment does not generate sufficient participation levels within 18 months, recruitment of patients and carers will be supplemented by:i.social media: advertisements via Meta (Facebook and Instagram) will include a brief description of the study e.g., ‘If you would like to try a web-program for people living with upper GI cancer or their carers, click here’. A link on the Meta advertisement will direct those interested to the iCare homepage for full study information; andii.participating health services’ oncologists or surgeons involved in the project. The clinician at participating sites will screen patients at outpatient clinical appointments and provide patients and carers with a flyer highlighting the details of the study and contact information of the project manager.

### Consent and screening

Once directed to the *iCare* website, participants will be invited to register by entering their name and email address. Following this they will be presented with the plain language statement for reading and then asked if they consent. Participants will have the option to invite either their carer (main support person) or the person living with cancer to join the study. Participants who would like to invite someone to join the study will be asked to provide the name, email address and phone number of the invitee and an automatically generated email invitation will be sent to them. Phone numbers are collected as a quality control measure to link participants together.

Potential participants will complete an online eligibility survey screening for age, type of cancer, and time since diagnosis. Eligible participants will receive an on-screen message informing them they are eligible. People who are not eligible will receive a message on screen thanking them for their interest in the study and referring them to the Cancer Council [name] telephone service [31] if they require support. Those eligible will be directed to the enrolment questionnaire via Qualtrics. After completing the enrolment questionnaire participants, carers or patients, will receive a follow-up email confirming their group allocation.

### Randomisation

The first member of the patient-carer dyad will be randomly assigned (1:1 ratio) to intervention or usual care (stratified by cancer type). If the 2nd member of the dyad consents, they will be allocated to the same arm as the other dyad member. To ensure that dyads are accurately allocated to the same arm, an embedded system within iCare will match email addresses and phone numbers provided during registration.

Consenting participants who do not sign up as part of a dyad (i.e., patients, carers or the patient-carer dyad) will be randomly assigned (1:1 ratio) to intervention or usual care (stratified by cancer type). The random sequence will be embedded in Qualtrics, ensuring allocation concealment. The biostatistician, co-investigators and associate investigators will be blinded to group allocation.

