#### Intervention group

Participants (patients and carers) allocated to the intervention arm will be automatically redirected to *iCare*’s main menu page after completing the enrolment questionnaire. This will allow for seamless entry into the program. Participants will also be sent an email with a link to the *iCare* program, a user identification number and instructions for how to download the program to their preferred device (ie, smartphone, tablet, laptop etc.) for future use. Video instructions on how to use *iCare* will be provided. Automatic email notifications will be sent weekly highlighting information and resources within *iCare*. Participants will be able to access *iCare* as needed (i.e., no frequency/module release/duration limits), allowing for observation of natural use. Participants will have continued access to *iCare* following completion of the study.

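### Allocation concealment does not extend to a dyad member who enrols after the other member's arm has been revealed

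*Protocol article*

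**What the plan says.** All references are to the protocol article.

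- **Who is randomised.** Under Randomisation, the first dyad member is allocated 1:1, stratified by cancer type. For the other: "If the 2nd member of the dyad consents, they will be allocated to the same arm as the other dyad member".
- **Who can be first.** Under Consent and screening: "Participants will have the option to invite either their carer (main support person) or the person living with cancer to join the study". Either role can therefore be the second member. Under Setting, one member may take part without the other, so joining second is a free choice.
- **When the invitation goes out.** Consent and screening describes it at the registration step: once contact details are given, "an automatically generated email invitation will be sent to them".
- **When the arm is revealed.** Consent and screening: "After completing the enrolment questionnaire participants, carers or patients, will receive a follow-up email confirming their group allocation". Under Intervention group, those allocated to iCare are also redirected automatically to its "main menu page after completing the enrolment questionnaire".
- **The safeguard claimed.** Randomisation: "The random sequence will be embedded in Qualtrics, ensuring allocation concealment". The only dyad-specific control is the matching of email addresses and phone numbers, which serves to put both members in the same arm.

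**The concern.** Concealment requires that nobody can know the arm when deciding whether to enter. The first member's arm is fixed and disclosed at the end of that person's own T1. The second member's consent and T1 have no stated deadline relative to that moment. Carers are defined under Selection criteria by their day-to-day involvement with the patient, so the arm can easily pass between the two, especially once one of them is using iCare.

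Three things are at stake for late second members:

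- Joining may depend on arm, so the arms may differ in who joins and not only in how many.
- T1 may not be a pre-allocation baseline, because it can follow household exposure to iCare or the knowledge that iCare is not yet available.
- Recruitment is part of the primary feasibility outcome, and a second-member rate that differs by arm is hard to carry into Phase III planning.

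The Analysis plan reports patients and carers separately. If patients usually register first, late joiners could make up a large part of the carer cohort and little of the patient cohort.

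**Working it through.** **1. Order of events, from the sections cited above**

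| Step | First member | Second member |
|---|---|---|
| a | Registers, consents, may name an invitee | Automatic invitation sent |
| b | Completes eligibility survey and T1 | May or may not have acted yet |
| c | Randomised; told by email; redirected if in iCare | May learn the arm from the first member |
| d | – | If not already enrolled: consents, completes T1, takes the pair's arm |

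Nothing in the article makes step c wait for the second member. A second member who enrols before c is concealed. One who enrols at d may not be.

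**2. The plan's own figure.** The sample size section gives 54 per arm, d = 0.54 and 80% power. With two-sided alpha 0.05 (assumed; not stated), 0.54 × √(54/2) − 1.96 = 0.846, and Φ(0.846) = 0.80. The figure reproduces and is not in dispute. It supplies the 54 per arm used below.

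**3. Illustrative size.** The article gives no second-member uptake, so every input here is an assumption: joining depends on a latent normal willingness correlated ρ with the outcome; the whole cohort joins late; there is no treatment effect; 54 per arm.

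Mean willingness among joiners at uptake p is m(p) = φ(z₁₋ₚ)/p. This gives m(0.8) = 0.350, m(0.7) = 0.497, m(0.6) = 0.644, m(0.5) = 0.798, m(0.4) = 0.966. The shift in outcome level between arms, in absolute value, is ρ × the difference in m. The standard error is √(2/54) = 0.192 SD.

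| Uptake, iCare v usual care | Difference in m | Shift, ρ = 0.2 to 0.5 | False-positive rate, level comparison |
|---|---|---|---|
| 60% v 60% | 0 | 0 | 5.0% |
| 60% v 50% | 0.154 | 0.03 to 0.08 SD | 5.3% to 6.9% |
| 70% v 50% | 0.301 | 0.06 to 0.15 SD | 6.1% to 12.3% |
| 80% v 40% | 0.616 | 0.12 to 0.31 SD | 9.8% to 36% |

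These shifts shrink roughly in proportion to the share who join late.

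**4. What the planned model does with this.** The Aims 2–3 analysis fits arm, time (T1, T2, T3) and their interaction, so the interaction compares change from T1. The bias in that contrast is (ρ at T2 − ρ at T1) × the difference in m. If willingness is equally correlated with T1 and T2, it is zero. With a gap of 0.1 in the 70% v 50% row it is 0.1 × 0.301 = 0.03 SD. Two things do not cancel: trajectories that differ between those who join in each arm, and a T1 already moved by exposure to iCare or by knowledge of the arm.

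**5. Recruitment.** If all 162 carers joined late at 70% and 50%, with equal numbers invited per arm, they would split about 94 to 68 (162 × 0.7/1.2 and 162 × 0.5/1.2). The pooled uptake of 60% would describe neither arm.

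**The case against.** A reader might infer that every second member enrols with the arm known. The article does not support that. The invitation is described at registration, ahead of the first member's T1, and the registry letter already invites carers. A prompt invitee can finish T1 before anything is disclosed. The study itself tells second members their arm only after their own T1, so earlier knowledge has to come through the first member: likely in a dyad, but not documented.

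A reader might also infer that the concealment sentence is simply false. It is sound for first members and for those who enrol alone, since they are drawn from the sequence. It does not reach late second members.

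It would also be too strong to say that the carer results are biased by a known amount, or that usual care gives little reason to join. Under Usual care group, those participants receive support information at enrolment and are offered iCare after 6 months, which may narrow any gap in uptake. The figures above rest on assumed uptake and describe outcome levels, not the planned contrast. Efficacy is preliminary in this phase II trial, and a difference in uptake by arm would itself be a reportable feasibility result.

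All of this limits the point without removing it. The unclear listing of dyads among those who do not sign up as a dyad, in the second paragraph of Randomisation, does not supply a holding step either.

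**Conclusion.** The point holds for any dyad whose second member enrols after the first member's allocation is revealed. For those people concealment is not ensured, joining may depend on arm, and T1 may not precede allocation. The comparisons exposed are the carer outcomes, the patient outcomes where the carer joined first, and second-member recruitment rates. First members and lone participants are unaffected.

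The size cannot be determined from the article. It is zero if uptake and selection are the same in both arms, and it falls with the share joining late. Stable level differences largely cancel in the time-by-arm contrast; differing trajectories and a shifted T1 do not. With feasibility and acceptability as the primary outcomes, this should be fixed but does not put the trial as a whole in doubt.

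**What to change.** 1. Where a registrant names an invitee, hold the pair's allocation and its disclosure until the invitee completes T1 or declines, or a short fixed window closes. Two weeks would match the follow-up interval already used under Setting and Data collection. Then randomise the pair once.
2. Second members who arrive later, or who were not named at registration, keep the pair's arm and stay in the main model. Record whether their T1 came before or after disclosure.
3. Report second-member uptake and T1 scores by arm. Add a sensitivity analysis restricted to participants whose T1 preceded disclosure. Dropping late joiners from the main model is not advised, as it could remove many carers.
4. Limit the concealment statement to participants who enrol before their pair's allocation is revealed.
5. If the system can no longer be changed, apply items 2 to 4 alone.

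**Cost.** One change to the allocation trigger, one recorded flag and a revised paragraph. First members who name an invitee wait up to two weeks. Because assessments are timed from enrolment, the protocol should then say whether that clock starts at T1 or at allocation. The sensitivity analysis will be less precise than the main model.

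### A patient and carer who register separately are not linked before randomisation, so the promised same-arm allocation of dyads is not secured

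*Protocol article*

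**What the plan says.** All references are to the protocol article.

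- **Same-arm rule (Randomisation).** "If the 2nd member of the dyad consents, they will be allocated to the same arm as the other dyad member". The stated means is that "an embedded system within iCare will match email addresses and phone numbers provided during registration".
- **Everyone else (Randomisation).** "Consenting participants who do not sign up as part of a dyad (i.e., patients, carers or the patient-carer dyad) will be randomly assigned", 1:1 and stratified by cancer type. The random sequence sits in Qualtrics.
- **What registration collects (Consent and screening).** "participants will be invited to register by entering their name and email address".
- **Naming a partner (Consent and screening).** "Participants will have the option to invite either their carer (main support person) or the person living with cancer to join the study". Only those who choose to do so "will be asked to provide the name, email address and phone number of the invitee". The purpose is given as follows: "Phone numbers are collected as a quality control measure to link participants together".
- **Direct entry.** On the registry letter, the Upper gastrointestinal cancer registry section says: "The invitation letter will also invite carers into the study". Patients and carers reach the website themselves by URL or QR code. Social media and clinical recruitment adds advertisements and flyers aimed at both.
- **Phone numbers elsewhere.** Data collection provides for telephone reminders, and Ethical considerations lists phone numbers among the stored participant details. Neither says when a participant's own number is obtained.

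**The concern.** The trial chose same-arm allocation for dyads, and that rule works only if the system knows who belongs to whom before it allocates. The described registration yields that knowledge only when one member volunteers the other's details. Where neither does, the pair falls under the rule for people not signing up as a dyad, and each is randomised alone.

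If the arms differ, a usual-care patient has a carer with access to iCare, or the reverse. Sharing of content would pull the arms together in both the patient and the carer comparison. Sample size and power calculation says the effect and variability estimates are to inform a Phase III trial, so a bias towards zero would carry forward. No step is described that would show how many such pairs exist.

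Two further points are unclear. The text does not say that matching in iCare precedes the draw in Qualtrics. The parenthesis defining those who do not sign up as a dyad includes the dyad itself.

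**Working it through.** **1. Three ways a pair can enter, followed as written**

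- *One member invites, and the partner registers with the email supplied.* The email match links them and the same-arm rule works.
- *One member invites, and the partner registers with a different email.* Linking then depends on the phone number. The inviter has given the partner's number, but the partner is described as registering with name and email only. Whether there is a number to compare depends on a collection step the article does not describe.
- *Both enter directly and neither invites.* Unless they happen to share an email address or phone, nothing matches. Collecting each person's own number would not help, because two people with separate emails and phones still have no common key.

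The third case is the real gap. Its cause is that identifying a partner is optional.

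**2. Chance of discordance**

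Treating the two 1:1 draws as independent, P(opposite arms) = 0.5 × 0.5 + 0.5 × 0.5 = 0.50.

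**3. Reproducing the plan's power figure**

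Inputs from Sample size and power calculation: 54 completers per arm and d = 0.54. Alpha is not stated; two-sided 0.05 is assumed.

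Power = Φ(d × √(n/2) − 1.96) = Φ(0.54 × √27 − 1.96) = Φ(0.846) = 80.1%. A t-test calculation gives 79.4%. The stated 80% reproduces.

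**4. Illustration of dilution**

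Let q be the share of pairs that enrol unlinked, m the share of patients with an enrolled carer, and c the share of the effect passed to an exposed usual-care participant. The protocol gives none of these.

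Diluted d = 0.54 × (1 − c × m × q/2)

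With m = 1:

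| q | discordant (q/2) | d, c = 1 | power, c = 1 | d, c = 0.5 | power, c = 0.5 |
|---|---|---|---|---|---|
| 5% | 2.5% | 0.526 | 78% | 0.533 | 79% |
| 10% | 5% | 0.513 | 76% | 0.526 | 78% |
| 20% | 10% | 0.486 | 71% | 0.513 | 76% |
| 50% | 25% | 0.405 | 56% | 0.473 | 69% |

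An m below 1 lowers the dilution. For example, q = 20% with m = 0.5 gives m × q = 10%, hence 76% power at c = 1.

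**The case against.** **Phone numbers.** A reader might infer that matching relies on phone numbers the study never collects. The documents do not support that. Invitees' numbers are collected expressly for linking, and registration can fairly be read as the whole sign-up flow, including the invitation. The telephone reminders and the list of stored details show that participants' own numbers are held. Email is also a matching key. What remains is that the two sections do not agree on whose numbers are collected and when.

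**Size.** A reader might also take a power loss of several points as a finding. It is not one. The unlinked share is assumed. Full transfer is an extreme bound, because iCare program content describes separate patient and carer pathways, with patient content steered by that patient's own reported needs. Patients may enrol without a carer. Nor do the eligibility criteria require a carer to live with the patient. The power figure itself concerns a secondary, preliminary aim; the primary outcomes are feasibility and acceptability.

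**Condensed article.** The invitation step and the same-arm rule show that dyads were considered, and the full protocol may list more form fields. That explains missing detail, but not the main point. The article states that inviting is optional, that direct entry is open to both, and that people not signing up as a dyad are randomised individually. Together these statements allow discordant pairs.

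**Parenthesis.** It is probably a drafting slip, since the preceding paragraph states the dyad rule clearly. It still needs correcting, because read literally it puts dyads under both rules.

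**Conclusion.** The concern holds for a defined group: pairs in which both members enrol directly and neither uses the invitation. As described, they are generally not linked, are randomised separately, and land in opposite arms half the time. That defeats the trial's own same-arm rule and can bias the preliminary estimates towards zero in both cohorts.

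How often this would happen cannot be derived from the protocol. The illustrative power of 78% (5% unlinked) to 71% (20% unlinked) assumes an enrolled carer for every patient, full transfer of effect, and two-sided alpha of 0.05. With smaller transfer or fewer enrolled carers the loss is less. No stated figure in the sample size section is wrong. The matter is worth correcting because the remedy is simple and the resulting bias would otherwise go unseen.

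**What to change.** 1. Before Qualtrics draws an allocation, require every registrant to do one of two things: enter a shared dyad code printed on the registry letter or flyer, or say whether their patient or carer has registered or may register and give that person's email and phone number. The second route is needed for people arriving from social media, who have no printed code.
2. State that the match runs before allocation, and keep the partner details so that a later registrant can be matched to someone already randomised.
3. Report the number of discordant pairs discovered after allocation.
4. Reconcile Consent and screening with Randomisation on whose phone numbers are collected and at which step.
5. Remove the dyad from the parenthesis in the second paragraph of Randomisation. Suitable wording would be: *patients or carers with no linked partner at the time of randomisation*. This can be applied when the first member is allocated, before it is known whether the second will consent.

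The cost is a small change to the registration form, letters and flyers, and an amendment submitted to the ethics committee. Sample size and design are unaffected.
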